#### Additional planned analysis

We will explore moderation of intervention effects by gender and age of the child, and type of caregiver. We are not measuring sex as a biological variable, so our analysis of sex differences is limited by a self-report gender of child indicated at baseline interview. While our aims are not powered to detect moderation effects, exploration of moderation in this RCT will serve as hypothesis generating and identify potential differing effects by gender and age to explore in future studies with larger sample sizes [80]. Moderators will be explored by adding a three-way interaction term to the models (e.g., Intervention Arm X Time X Moderator). This three-way interaction coefficient indicates whether change in average outcome varies by levels of the moderator while controlling for change in the control group. When a three-way interaction term is significant, we will re-estimate the models, stratified by level of the moderator, to generate strata-specific effect sizes. Using the gender model as an example, and significance set to *p* = 0.05, assuming ~ 50% of our child sample will be male, with our sample size of *n* = 30 male and *n* = 30 female children enrolled in Little Holy One, we will have 80% power to detect a medium (f = .24) difference in intervention effects between genders.

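### Effects by moderator level are produced only after a significant three-way interaction, which selects exaggerated differences in an analysis meant to generate hypotheses

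*Protocol article*

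**What the plan says.** The rule stands in the Protocol article, Sample size and power, under Additional planned analysis. The first step is unconditional: "Moderators will be explored by adding a three-way interaction term to the models (e.g., Intervention Arm X Time X Moderator". The second is conditional: "When a three-way interaction term is significant, we will re-estimate the models, stratified by level of the moderator, to generate strata-specific effect sizes".

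The same paragraph gives the purpose. Exploring moderation "will serve as hypothesis generating and identify potential differing effects by gender and age to explore in future studies with larger sample sizes". It also concedes the limits of the sample: "While our aims are not powered to detect moderation effects". It then works a gender example, with "significance set to *p* = 0.05", using the intervention arm: "with our sample size of *n* = 30 male and *n* = 30 female children enrolled in Little Holy One", from which "we will have 80% power to detect a medium (f = .24) difference in intervention effects between genders". Table 4 repeats f = 0.24 at N = 60 for gender, age and type of caregiver.

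Nowhere does the article provide for effects within moderator levels when the interaction is not significant.

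**The concern.** Someone planning a larger trial needs the estimated arm effect at each moderator level and an interval around it. That need is greatest when the present data are imprecise. The stated rule supplies those figures only when the observed difference between levels is large relative to its standard error. In a sample that is small for interactions, that condition is met mostly when chance has pushed the strata apart.

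Two things follow. For most moderators no stratum effects will be produced. Where they are produced, one stratum will tend to look better than it is and the other worse, possibly as if it had no benefit or were harmed. Figures of that kind could steer a later trial towards, or away from, boys or girls, an age group or a type of caregiver.

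**Working it through.** **Inputs from the protocol.** 120 dyads randomized 1:1; 5 assessments; ρ = 0.3; 30% attrition; overall effect f = 0.13; gender example with 30 + 30 children in one arm, α = 0.05, 80% power at f = 0.24.

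**Assumptions.** Two-sided test; two equal strata, so 30 dyads per arm-by-moderator cell; d = 2f for two equal groups; a mean-level 2 × 2 contrast standing in for the three-way term; average arm effect d = 2 × 0.13 = 0.26. The protocol gives no true difference between strata, so I vary it.

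**1. The plan's own figures.** The design effect is 1 + (5 − 1) × 0.3 = 2.2, and 420 / 2.2 = 190.9, which agrees with the stated 190. For the gender example, effective n per group = 30 × 5 / 2.2 = 68.2. With d = 0.48, 0.48 / √(2/68.2) = 2.80, and power = Φ(2.80 − 1.96) = 0.80. The stated 80% therefore reproduces, but as 30 against 30 within the intervention arm and without dropout. With 30% attrition, effective n is 47.7 per group and power is 0.65.

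**2. The contrast that decides whether strata are estimated.** This is the difference between strata in the arm effect, and it uses four cells. With attrition, each cell has 30 × 5 × 0.7 / 2.2 = 47.7 effective observations (4 × 47.7 = 190.9 in all). So SE = √(4/47.7) = 0.29, and the observed difference must exceed 1.96 × 0.29 = 0.57 SD.

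**3. How often the trigger fires, and what it selects.** Let I be the true difference, λ = I/SE, c = 1.96, P₊ = Φ(λ − c), P₋ = Φ(−λ − c).

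- Probability of firing: P = P₊ + P₋.
- Overstatement of the difference: [λ(P₊ − P₋) + φ(c − λ) + φ(c + λ)] / (λP).
- Stratum effects: with equal strata, the mean of the two stratum estimates is independent of their difference. Given firing, they therefore average 0.26 ± ½ × SE × [λ + (φ(c − λ) − φ(c + λ)) / P]. A simulation of 2,000,000 draws gives the same values.

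For I = 0.24, λ = 0.24/0.2895 = 0.829, P₊ = 0.129 and P₋ = 0.003, so P = 0.132. Results with 30% attrition (effective size 190.9):

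| True difference (d) | Trigger fires | Difference overstated | True stratum effects | Mean stratum effects when it fires | Larger stratum overstated |
|---|---|---|---|---|---|
| 0.24 | 13% | 2.96 | 0.38, 0.14 | 0.60, −0.08 | 1.58 |
| 0.36 | 24% | 2.05 | 0.44, 0.08 | 0.63, −0.11 | 1.42 |
| 0.48 | 38% | 1.60 | 0.50, 0.02 | 0.64, −0.12 | 1.29 |

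**4. Sensitivity.** Without attrition SE = √(4/68.2) = 0.242. The trigger then fires in 17%, 32% and 51% of trials, the difference is overstated 2.5, 1.75 and 1.4 fold, and the larger stratum effect 1.46, 1.31 and 1.19 fold. If the stated 80% power at f = 0.24 is taken at face value, the overstatement of the difference is only 1.12 fold at f = 0.24, but 1.85 fold at f = 0.12 (power 29%).

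**The case against.** The strongest reply has four parts.

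- **The interaction is always fitted.** A reader might infer that moderation is estimated only when significant, or that non-significant results will be withheld. The text supports neither. The three-way coefficient, which directly estimates the difference in effects, is fitted for every moderator, and nothing says its estimate or interval will be suppressed. This part stands: only the effects within levels are conditional.
- **Subgroup effects are not inflated two- to three-fold.** A reader might carry the factor for the difference over to the stratum effects. In the calculation, two- to three-fold belongs to the difference between strata, and only at the smaller assumed true differences. The larger stratum effect rises by clearly less, and the smaller one falls. This part stands too, and so does the caution that every factor depends on a true difference the protocol does not give.
- **The calculation is a stand-in.** The planned term concerns change over time, child age has three levels in the randomization section, and equal caregiver groups are not promised. The figures show the mechanism and its rough size; they are not properties of this trial.
- **Testing interaction first is good practice, and the analysis is already labelled exploratory.** The test does protect against false subgroup claims, and the label lowers the stakes. But that protection comes from how claims are worded. It does not require withholding the stratum estimates. The proposed change keeps the test and removes only its use as a filter on what is estimated.

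The stated 80% power does not rescue the rule. That figure omits the control arm and dropout. For the arm-by-gender contrast at the same f = 0.24, power is 51%, or 38% with the protocol's 30% attrition.

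**Conclusion.** The point holds in a limited form. The rule for producing effects within moderator levels conflicts with the purpose the protocol gives for the analysis. Under the assumptions above, for true differences of d = 0.24 to 0.48 with the planned attrition, stratum effects would be produced in roughly one trial in eight to three in eight. They would then show too wide a gap: one stratum moderately overstated, the other at about zero or below. The direction of this selection does not depend on the assumed values, but its size does.

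The documents do not support saying that moderators missing significance get no estimate, or that subgroup effects will be two- to three-fold too large. Severity is minor: the analysis is secondary and exploratory, and the primary comparison is untouched.

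**What to change.** In Additional planned analysis, replace the significance-triggered stratified refits. For each named moderator, report the interaction estimate and the arm effect at every moderator level, with 95% intervals, from the single interaction model fitted to all participants, whatever the interaction p-value. Keep the interaction test as the basis for any statement that effects differ, and label the results exploratory.

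The single model already contains these effects, so no further data, participants or model fits are needed. The cost is a few more table rows.

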### Data collection methods

Data will be collected and managed in a REDCap database [49, 50]. All questionnaires are built in REDCap and data are directly entered by the participant or the evaluator. The evaluator will be trained on both the function of REDCap and the purpose and execution of each study instrument as well as open and sensitive interviewing methods.

The study schedule is designed to retain participants through all 12 intervention lessons and a range of evaluation time points. Gift card incentives will be given at each evaluation session. Study-related gifts and necessary supplies, such as smudging materials and notebooks at intervention lessons and food supplies and recipes at control lessons, will be provided. We have allocated one Head Start semester (total of 16 weeks) to complete the 12-week intervention or control session, providing an additional time to complete any make-up sessions and to account for any delays related to illness. Participants who discontinue or deviate from the intervention protocol will continue to complete the assessments as planned unless they withdrawal from the study. If a participant chooses to leave the study, they will not be provided with further intervention or control sessions. Enrolled participants will also be referred to appropriate resources, as needed, throughout the study.

### Statistical methods

#### Aim 1

The primary effectiveness aim will be assessed on a full intent-to-treat basis. The design incorporates longitudinal measurements that led to a nested data structure. For Aim 1 there are 5 repeated assessments (level-1) nested within children and caregivers (level-2) nested with 4 community health workers (level-3). Given the complexities of nested data, we will use mixed-effects regression models to analyze the data. Mixed-effects regression models are highly flexible and accommodate variability in the number and spacing of assessments within and across participants, continuous and discrete outcome distributions, varied patterns of change over time (e.g., quadratic), and phase-specific change (i.e., discontinuous or piecewise change [79, 81, 82]. To build our outcome models, we will first explore outcome trajectories graphically and descriptively evaluated to determine the best distribution for modeling using “spaghetti plots.” We will then iteratively build our estimation models using the approach described in Singer and Willett [83]. The first model will estimate the proportion of outcome variance at each level; the second model will add growth terms; the third model will add fixed-effect indicators to test for differences in baseline characteristics if necessary [83]. If there are differences in baseline characteristics between the intervention groups, these will be statistically controlled in models that follow. The fourth, and final, model will add the condition indicator (i.e., 0 = WLC, 1 = Little Holy One) and cross-level interaction effects between condition and level-1 terms.

#### Aim 2

We will again use mixed-effects regression models to analyze the outcomes. Mixed-effects regression models can evaluate phase-specific change while maintaining statistical power. This is essential for evaluating SCEDs due to the repeated measurements of the primary outcomes within each phase; and the interventions (i.e., delivery of cultural components) occurring at different time points within these phases. The key features of a SCED are that a) each participant will have a series of repeated measurements on the primary outcome; (b) the measurements occur across multiple experimental time periods, known as phases; and (c) each participant serves as its own comparison group as he/she progresses through the phases. This design is highly flexible and robust to unanticipated events (e.g., disruption in home life such as moving, etc.). Longitudinal assessments make it possible to straightforwardly model and control for these types of events by using time-varying indicators. Further, the use of multilevel models will partition the outcome variance into components specifically attributable to variability over time and across phases. Likewise, in a SCED everyone has their own starting value, yielding individual-specific outcome trajectories that are adjusted for unanticipated events occurring over time. As a result, it is possible to provide a strong evaluation of the impact of additional cultural components on individual trajectories of change while in the intervention.

A similar model building approach will be used including initially examining trajectories of session-by-session scores on the PSS, followed- by incremental model building like Aim 1. The final model will add the time-varying condition indicators (i.e., 0 = no cultural component; 1 = cultural component) and interaction effects between condition and the linear terms for change over time. This approach will create distinct sub-phases for each participant: before the component was delivered and after the component was delivered. Statistically, this modeling approach allows for determination of whether there is a shift in the overall level of the outcome or in the slope of the outcome following the delivery of the cultural component.

#### Aim 3

We will explore the bivariate associations between parent social network characteristics and suicide risk and opioid use. After a foundational understanding of the bivariate relationships is established, we will use generalized linear regression models to investigate the multivariate relationships between individual network characteristics on the outcomes of suicidal behaviors and opioid use. Additionally, we will assess the effect of Little Holy One on individuals’ social networks. The literature continues to support the use of social network measures as predictors of behavioral outcomes yet is less clear when it comes to the role behavioral interventions have on individuals’ social networks [75, 76]. We hypothesize that individuals that are randomized to the intervention group will see a significant positive change in their network composition compared to those in the control arm of the study due to the culturally salient nature of the content of the intervention arm. To assess this, we will use the pre-intervention data and the initial post-intervention data to assess changes in social networks over time between treatment groups.

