### Allocation, concealment, and implementation

The intervention allocation sequence will be generated using the “ralloc” command in Stata with 7 total strata (3 for age, 2 for gender, and 2 for site), a date-based randomization seed, and blocked randomization with blocks of varying size (8–16). Participants will be stratified by Head Start site, child gender, and child age to ensure equal groups of 3, 4, and 5 years old in each of the conditions. If more than one child in a family meets eligibility criteria, we will randomly select which child gets included in the study. We are unable to block randomize by parent gender because local feedback has suggested the majority are women.

Allocation will be handled by Research Electronic Data Capture (REDCap) electronic data capture tools hosted at Johns Hopkins University [49, 50]. The project data manager will generate the allocation tables describing the randomized order of allocation and upload them into REDCap’s randomization module, which will then implement all allocation. Once uploaded, REDCap will not allow the allocation tables to be accessed; thus, the allocation process will be concealed and protected from error. All evaluators will be blinded to participants’ study assignment and would only become unblinded if essential for management of the participant.

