***Aim 1:***
*To evaluate the effectiveness of community health worker delivered Little Holy One on parent and child behavioral and mental health outcomes, using a randomized controlled trial design.*

Primary outcomes – Parent:Change in parent trauma symptoms will be self-reported at 2 weeks to 24 months using the *Post-Traumatic Stress Disorder (PTSD) Checklist for the Diagnostic and Statistical Manual of Mental Disorders (DSM) -5* (PTSD Checklist for DSM-5, Civilian Version) [51].Change in caregiver parenting stress will be self-reported using the *Parenting Stress Index – Short Form* (PSI-SF). The PSI-SF is a 36-item self-report that measures three domains of parenting stress: parental distress, parent-child dysfunctional interaction, and difficulty with child [52]. Scores range from 36 to 180. Score ranges are represented as percentiles; 15–80 is considered a typical stress percentile, 81–89 is considered a high stress percentile, and 90–100 is considered a clinically significant stress percentile. The PSI-SF was used in previous studies with Native American populations and performed well [27, 31, 34, 35].

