### Sample size and power

#### Aim 1

We based our primary sample size calculation on previous Family Spirit results indicating small to medium effect sizes for adult and child socio-emotional and behavioral outcomes 6 months post intervention completion [27, 31]. As such, power is based on detecting a small-medium difference between Little Holy One and control participants on caregiver and child outcomes 6-months post intervention completion (see below for power at 24 months post intervention). Since power analysis for mixed-effects regression models is complex, we use the approach described by Hox and Hedges [78, 79]. In this approach there are three steps: 1) estimate the power for a single-level regression model, ignoring clustering. This is considered the target sample size; 2) Compute the actual sample size for the proposed study that ignores the impact of clustering and accounts for attrition; and 3) Generate the effective sample size by penalizing the actual sample size with the design effect formula (i.e., n_eff_ = n / [1 + {n_clus_ – 1} ρ]). If the effective sample size is equal to or larger than the targeted sample size, then power is considered sufficient to detect the effect of interest. In our case, for step 1 power is .80 to detect a medium effect of f = .18 with 120 single-level, independent observations. For step 2, our actual sample size of 120 caregivers and children, with 5 measurement points, yields 600 (non-independent) observations. Accounting for attrition based on our previous work with family-based prevention interventions (i.e., the final *Family Spirit* trial had 18% attrition after 39 months’ intervention) [34], we used a conservative 30% attrition rate and adjusted our actual sample size to 420 non-independent observations. For step 3, using the design effect formula, accounting for 30% attrition and assuming a conservative nesting effect of ρ = 0.3 (to account for additional nesting within schools), our actual sample size of 420 non-independent observations provides the statistical power of 190 independent observations as our effective sample size. The effective sample size is more than the estimate for the targeted sample size indicating sufficient power to detect a small effect (f = .13). Sample size calculations for *all* aims can be found in Table 4**.**

**Table 4 Tab4:** Sample size calculations

	N	α	Power (1-β)	Effect size (f)

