#### 24-month outcomes

While not our primary outcome, based on our conceptual framework, effects on proximal outcomes should correspond to effects on more distal outcomes measured at 2 years post-intervention. As there are no other longitudinal follow-up intervention studies in Native American settings, we assume a very conservative 50% retention rate of our original enrolled sample. This will result in approximately *n* = 42 participants in each arm at *24-months post intervention* completion. With power set to 80% and alpha set to 0.05, with *n* = 42 participants in each arm, and an additional 2 assessment time points, we will be able to detect an average effect size of f = 0.20 (medium effect) on continuous outcome measures between the groups.

#### Aim 2

Using the same approach as our Aim 1 power calculation, we will be powered to detect a medium effect (f = 0.20) in level of perceived stress (PSS) following delivery of the cultural components.

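### The Aim 1 model picks its covariates from chance baseline differences, leaves out the stratification factors, and names no contrast for the 6-month difference used for power

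*Protocol article*

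**What the plan says.** Under Statistical methods, Aim 1, the protocol article plans a mixed-effects regression built in steps. Before modelling, "we will first explore outcome trajectories graphically". The first model then partitions the variance, the second adds growth terms, and the third tests for baseline differences if that is thought necessary. The covariate rule is: "If there are differences in baseline characteristics between the intervention groups, these will be statistically controlled in models that follow". It gives no list of characteristics and no threshold. The fourth and final model adds the condition indicator together with "cross-level interaction effects between condition and level-1 terms". The section mentions quadratic, discontinuous and piecewise change as forms that mixed models can accommodate, and commits to none.

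Under Allocation, concealment, and implementation: "Participants will be stratified by Head Start site, child gender, and child age". None of the three factors is named in the Aim 1 model. Child gender and age return only as exploratory moderators under Additional planned analysis.

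Under Sample size and power, Aim 1: "power is based on detecting a small-medium difference between Little Holy One and control participants on caregiver and child outcomes 6-months post intervention completion". The primary outcome definition spans all of follow-up: "Change in parent trauma symptoms will be self-reported at 2 weeks to 24 months".

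**The concern.** Baseline differences between randomised arms are chance by construction, so testing for them says nothing that should decide the model. A variable that differs by chance but is unrelated to outcome is adjusted for. A strongly prognostic variable that happens to be balanced is left out, and the precision it would have bought is lost. Two analysts following the rule could fit different primary models, because the characteristics and the threshold are open.

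The rule also works against the stratified design. The factors thought important enough to stratify on are those that stratification keeps from differing, so they are the least likely to be adjusted for.

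A second looseness adds to this. The growth terms are settled during iterative building on outcome data. No term of the final model is tied to the difference at 6 months post intervention that the power section describes. The reported primary result could therefore be any of several coefficients.

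**Working it through.** **1. The plan's own figure.** The covariate rule carries no figure. The only related one is the Aim 1 power statement, used here solely to see which comparison it concerns. Inputs from Sample size and power: 120 dyads, 5 measurements, 30% attrition, ρ = 0.3.

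- Observations: 120 × 5 × 0.70 = 420.
- Effective sample size: 420 / [1 + (5 − 1) × 0.3] = 420 / 2.2 = 190.9, which reproduces the stated 190.
- The comparison described is an arm difference in outcome 6 months after the intervention ends.

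Whether the stated detectable effects follow from these sample sizes is a separate matter and is not argued here.

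**2. How often chance alone changes the model.** The article states no threshold, so .05 per test is assumed, with independent tests. Then P(at least one significant) = 1 − 0.95^k.

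| k | Probability |
|---|---|
| 5 | 1 − 0.774 = 0.23 |
| 10 | 1 − 0.599 = 0.40 |
| 20 | 1 − 0.358 = 0.64 |

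Table 3 marks 20 instruments or records at baseline, before any demographic item, so k = 20 is not extreme. Many of these measures are correlated, which would lower the probability for a given k.

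**3. Whether the stratification factors can enter.** Site has 2 levels, child gender 2 and child age 3, giving 12 crossed cells. Stratified blocks of 8 to 16 were simulated with 120 dyads and equal cells (assumed, so 10 per cell). In 4,000 simulated trials no stratification factor differed between arms at p < .05. Balance is not exact, because cells can end in an incomplete block, but it is far too close for the rule to pick these factors up.

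**4. What leaving them out does.** If balanced factors explain a share R² of outcome variance, an unadjusted analysis overstates the error variance of the arm difference. Under perfect balance the type I error is 2 × [1 − Φ(1.96 / √(1 − R²))]. The simulation allows for the imperfect balance of unfinished blocks and so lies slightly higher.

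| R² (assumed) | Perfect balance | Simulated, unadjusted |
|---|---|---|
| 10% | 0.039 | 0.040 |
| 20% | 0.028 | 0.032 |
| 30% | 0.019 | 0.024 |

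With the factors in the model, the simulated error returns to about 0.05. The test as planned is therefore conservative, and the loss is in precision.

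**5. Which term is the primary test.**

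- Power section: arm difference at 6 months post intervention.
- Outcome definition: change over 2 weeks to 24 months, with no time point singled out.
- Final model: condition, plus condition by level-1 terms, with the form of those terms left open.

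A difference at 6 months post intervention is a combination of the condition coefficient and the interaction coefficients evaluated at that time. It can be computed once time is coded and its form is fixed. Nothing in the article says that this combination is the primary test.

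**The case against.** The best defence is that this is a condensed article. A full covariate list and the exact contrast could sit in an analysis plan that is not shown, and several of the remedies are choices among valid methods. That stands for anything the article merely leaves out. It does not cover the covariate rule, which is stated and is faulty as stated. It does soften the point about the contrast, which is best read as something to pin down.

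Four stronger readings are tempting and are not supported:

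- *The model cannot test the mean difference.* The final model contains the condition indicator as well as the interactions, so the 6-month difference is derivable. The gap is that it is not designated.
- *A slope test would miss a sustained benefit, so power is very low.* That presumes a purely linear condition-by-time test. The article names quadratic and piecewise forms as possible and commits to none. The size of any loss also depends on the unknown pattern of effect.
- *The growth shape is chosen from the plots.* The stated purpose of the plots is to settle the distribution for modelling. Choosing the shape is a fair inference from the iterative building, but it is not the text.
- *The two primary outcomes are each tested at .05 without control.* The article states no testing rule. The .05 appears as a power input, and a multiplicity procedure is commonly left to the analysis plan.

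Nor does omitting the stratification factors create false positives. The error goes the other way, as step 4 shows.

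**Conclusion.** The concern holds in a limited form. The article fixes a covariate rule for the primary analysis that depends on chance imbalance and in practice excludes the factors the randomisation was stratified on. By chance alone the rule would alter the model in 23% to 64% of trials for 5 to 20 comparisons, assuming independence and a .05 threshold. Omitting the stratification factors lowers the type I error to about .040 to .024, assuming that they explain 10% to 30% of outcome variance, that strata are of equal size and that all 12 cells are crossed. The documents give no figure for how prognostic these factors are, so the precision lost could be small.

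The open form of time and the missing designation of a primary contrast are a lesser, related gap. The planned model can deliver the powered comparison, but the text does not commit to it.

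**What to change.** - Delete the test of baseline differences and the rule that adjusts for whatever differs.
- State that site, child age and child gender are always in the Aim 1 model, and that the analysis conditions on the baseline outcome score.
- Fix the form of time before any outcome is seen, for example visit as a category with arm by visit.
- Name the between-arm difference at 6 months post intervention as the primary contrast, and say which visit in Table 3 that is. If months are counted from baseline and the intervention ends at 12 weeks, 6 months post intervention falls at about 9 months, where Table 3 has no visit.
- Keep the growth-curve models as secondary analyses.

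The change is to wording only. Site takes 1 degree of freedom, gender 1 and age 2, which makes 4, or 5 with the baseline score. That is slight with 120 dyads.

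Naming the contrast makes the test explicit but does not supply power. With 42 per arm after 30% attrition and d = 2 × 0.18 = 0.36, the standardised difference is 0.36 / √(2/42) = 1.65. Two-sided power at .05 is then about 0.38. Conditioning on a baseline score correlated 0.3 with the outcome (assumed) gives 1.65 / √(1 − 0.09) = 1.73, or about 0.41.

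### Aim 1 covariates are chosen by observed baseline differences between arms, a rule that follows chance and will rarely admit the site, child-age and child-gender strata

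*Protocol article*

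**What the plan says.** Under Statistical methods, Aim 1, the article builds the mixed model in four steps. The first two estimate variance components and add growth terms. In the next, "the third model will add fixed-effect indicators to test for differences in baseline characteristics if necessary". The consequence of that step is then stated: "If there are differences in baseline characteristics between the intervention groups, these will be statistically controlled in models that follow". Treatment condition, with its interactions with the within-person terms, comes in only at the last step. The levels named are assessments, children and caregivers, and four community health workers.

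Under Allocation, concealment, and implementation the article says: "Participants will be stratified by Head Start site, child gender, and child age to ensure equal groups". None of these three factors is named in the Aim 1 model. Child age and child gender return only as exploratory moderators under Additional planned analysis.

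Under Sample size and power, Aim 1, the value ρ = 0.3 is justified partly "to account for additional nesting within schools". The Participants section says that two Head Start centres take part.

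**The concern.** The rule picks covariates by imbalance. When allocation is random, an imbalance says nothing about whether a characteristic predicts the outcome, which is the reason for adjusting. The adjusted set, and so the estimate, then turns on which characteristics happened to differ in this sample.

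The rule also works against the design. Stratified blocks exist to make the arms alike on site, child gender and child age, so a rule triggered by unlikeness will seldom select them. If those factors relate to how the outcome changes, an unadjusted analysis keeps their variance in the standard error although the design has already taken much of it out of the comparison. The reported standard error is then too large and power is lost.

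**Working it through.** **1. The plan's own figure.** The effective sample size is the one stated number that carries the school-nesting assumption.
- Observations: 120 × 5 = 600. After 30% attrition: 600 × 0.7 = 420.
- Design effect: 1 + (5 − 1) × 0.3 = 2.2.
- Effective size: 420 / 2.2 = 190.9. The article states 190, so it reproduces.

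The cluster size that gives this is 5, the repeated assessments within a person. Schools enter only through the choice of ρ.

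**2. How often the rule would admit a stratification factor.** The article sets no threshold for a difference, so I assume a baseline test at p < 0.05. Simulated settings: 120 dyads, 1:1, age (3 levels), gender (2) and site (2) fully crossed to 12 cells, permuted blocks of 8 to 16. Any of the three factors entered the model in under 0.1% of runs. On that assumption the rule amounts to omitting the strata.

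**3. Cost of leaving them out.** Let R² be the share of between-person variance in change that the strata explain. The documents do not give it, so it is shown from 0 to 0.15. Table 4 gives α = 0.05 and power 0.80; I assume a two-sided test. The adjusted statistic then has mean 1.960 + 0.842 = 2.802 and SD 1.

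- Strata well balanced: the unadjusted statistic has mean 2.802√(1−R²) and SD √(1−R²). Type I error = 2[1 − Φ(1.96/√(1−R²))]. Power = Φ(2.802 − 1.96/√(1−R²)).
- Balance not achieved: SD is 1 and type I error stays at 0.05. Power = Φ(2.802√(1−R²) − 1.96).

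For R² = 0.10, √0.90 = 0.949 and 1.96/0.949 = 2.066. Type I error = 2[1 − Φ(2.066)] = 0.039. Power = Φ(0.736) = 0.769 if balanced, and Φ(0.698) = 0.757 if not.

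| R² | Type I error, balanced | Power, balanced | Power, not balanced |
|---|---|---|---|
| 0 | 0.050 | 0.80 | 0.80 |
| 0.05 | 0.044 | 0.785 | 0.780 |
| 0.10 | 0.039 | 0.769 | 0.757 |
| 0.15 | 0.034 | 0.750 | 0.733 |

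**4. Check by simulation.** Same allocation, one outcome per person, linear model, 8,000 null runs and 4,000 runs at an illustrative standardised difference of 0.515. Here R² is the share of variance in that single outcome, and total variance is held fixed, so adjusted power rises with R².

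| R² | Type I error: rule / strata always in | Power: rule / strata always in |
|---|---|---|
| 0 | 0.053 / 0.052 | 0.79 / 0.78 |
| 0.1 | 0.043 / 0.052 | 0.81 / 0.84 |
| 0.2 | 0.036 / 0.052 | 0.82 / 0.87 |
| 0.3 | 0.024 / 0.050 | 0.82 / 0.91 |

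The direction agrees with step 3. These losses overstate what to expect here. The plan tests condition by time with repeated measures per person, and stable stratum differences in level largely drop out of that contrast. Only a relation of the strata to change, or to dropout, carries over.

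**The case against.** The strongest reply is that the article condenses a fuller protocol, that covariate lists usually sit in the analysis plan, and that nothing in the text bars the strata. It is right that the text does not forbid them. A reader might infer that the plan excludes them outright, or that the design section requires them in the analysis. Neither is written: the stated purpose of stratifying is equal groups, and analysing as randomised is a statistical principle, not a sentence in this document. What remains is that the article does state a rule for entering covariates, and that rule is poorly chosen. This corrects a stated rule and does not fill a silence.

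A second reply is that the primary outcomes are parent trauma symptoms and parenting stress, while two of the three strata are child characteristics. The share of variance in parental change that they explain may be close to zero, and at zero nothing is lost. This stands, and it is why the range starts at 0. The case is more plausible for child behaviour and attendance, which are secondary.

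A reader might also infer that the model wrongly omits a school level, since the power section expects nesting within schools. The documents do not support that as a separate error. Only two centres take part, so a random school effect could not be estimated usefully. Dyads are randomised within site, so omitting site does not inflate type I error. A cautious ρ in a power calculation does not contradict the model.

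Finally, the exploratory moderator models do use child age and gender, but as tests of differing effects and not as adjustment in the main analysis.

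**Conclusion.** The point holds as a matter of precision and prespecification. Selecting Aim 1 covariates by baseline difference makes the adjusted set depend on chance and will in practice rarely admit site, child gender or child age. With an assumed 0 to 15% of variance in change explained by the strata, power that would be 80% with adjustment lies between 80% and about 73–75%, and true type I error between 5% and about 3.4%. The sizes rest on that assumed share, on a two-sided 5% test and on a large-sample approximation. A reader might infer biased estimates or too many false positives; the direction is the opposite, towards a conservative test. The change is worth making because it costs almost nothing, not because the trial's conclusions are at risk.

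**What to change.** In Statistical methods, Aim 1, replace the baseline-difference rule with prespecified fixed effects for Head Start site, child age group and child gender in the Aim 1 models, whatever balance is observed. Add their interactions with the planned growth (time) terms, because main effects alone would change the condition-by-time test little. Drop the step that tests baseline differences to choose covariates, and present baseline comparisons descriptively only. The fixed site effect also covers the two schools, so no separate school level is needed.

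The factors are already recorded for randomisation. The cost is 1 (site) + 2 (age) + 1 (gender) = 4 main-effect degrees of freedom, plus 4 for each growth term: 8 in all with linear time, 12 with linear and quadratic time. Crossing the strata with categorical visits should be avoided. It would add 4 × (5 − 1) = 16 interaction terms for five assessments, or 4 × (7 − 1) = 24 for the seven main time points in Table 3, which is heavy for 120 dyads.
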